## Criteria for premature withdrawal

Subjects have the right to withdraw from study treatment at any time for any reason.

In the case that the subject decides to prematurely discontinue study treatment (“refuses treatment”), all efforts will be made to complete and report the observations prior to withdrawal as thoroughly as possible preferably by returning to site to complete assessments as per the Week 96 visit and the Treatment Completion CRF.

If possible, a complete final evaluation at the time of the subject’s withdrawal from the study should be made with an explanation of why the subject is withdrawing from the study. When applicable, subjects should be informed of circumstances under which their participation may be terminated by the investigator without the subject’s consent/assent. The investigator may withdraw subjects from the study in the event of intercurrent illness, AEs, pregnancy, lack of compliance with the study and/or study procedures (e.g., dosing instructions, study visits) or any reason where it is felt by the investigator that further follow-up of the subject is impossible or it is in the best interest of the subject to be terminated from the study. Any administrative or other reasons for withdrawal must be documented and explained to the subject.

If the reason for removal of a subject from the study is an AE, the principal specific event will be recorded on the CRF. The subject should be followed until the AE has resolved, if possible.

An excessive rate of withdrawals can render the study non-interpretable; therefore, unnecessary withdrawal of subjects should be avoided.

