| Co-Investigator: | [name], [name], [name], [name], [name], [name] |

SYNOPSIS OF PROTOCOL

| TITLE | Combination therapy of pegylated interferon-alpha-2b, nucleoside/nucleotide analogues (NAs) and GMCSF in NA-experienced chronic hepatitis B patients: A prospective, randomized open-label trial (Anchor study) |
| --- | --- |
| SPONSOR | The Chinese National Thirteenth Five Years Project in Science and Technology (2017ZX10202201) |
| INDICATION | NA-experienced CHB |
| OBJECTIVES | Primary: To compare the efficacy (HBsAg loss) and safety of pegylated interferon alfa-2b therapy plus entecavir (ETV) with or without GMCSF or ETV alone in NA-experienced CHB patients who had sustained HBV DNA suppression by ETV treatment. |
| TIRAL DESIGN | A multi-center, randomized, prospective, open-label Phase IV clinical trial. Patients will be randomized 1:1:1 in the IFN+ETV +GMCSF combination therapy group, IFN+ETV group or ETV group. |
| NUMBER OF PATIENTS | Total N 257 |
| TARGET POPULATION | The subjects who pre-treated by ETV for at least 1 year and achieved HBV DNA ≤10^3^ copies/ml & HBsAg <3000 IU/ml. Patients were excluded if they had previously developed drug resistance to ETV, or received IFN or systemic antiviral therapy within the previous 6 months. Patients were also excluded if they were coinfected with the human immunodeficiency virus, hepatitis C virus or hepatitis D virus or if they had decompensated liver disease (defined as a Child-Pugh Score B or C), pregnancy or lactation, or any other contraindication for IFN therapy |
| LENGTH OF STUDY | 96 weeks treatment  24 weeks follow up |
| DURATION OF STUDY | 42 months after first patient randomized |
| INVESTIGATIONAL PRODUCTS  DOSE/ROUTE/REGIMEN | Group 1: Entecavir 0.5mg once per day; P.O.  Group 2: Entecavir 0.5mg once per day (cessation at week 48); P.O. Pegylated interferon alfa-2b 180ug once per week; S.C.  Group 3: Entecavir 0.5mg once per day (cessation at week 48); P.O. Pegylated interferon alfa-2b 180ug per week; S.C. plus GM-CSF (Teerli, Xiamen Amoytop Biotech Co., Ltd, China) 75 μg once-daily for the first 5 consecutive days each month; S.C. |
| ASSESSMENT OF EFFICACY | Primary Endpoint:  HBsAg loss at Week 96.  Secondary Endpoint:   1. HBsAg seroconversion 2. Proportion of patients who achieve undetectable HBV DNA 3. Quantitative HBsAg measurement 4. HBeAg seroconversion 5. ALT normalization 6. Sustained virologic response at the end of follow-up |

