GM-CSF has the following applications in the treatment of hepatitis: (1) to treat CHB combined with IFN; (2) to treat chronic hepatitis C; (3) to be used as an adjuvant for hepatitis B vaccine; (4) to be used in hepatitis patients undergone IFN therapy with bone marrow suppression. It is safe and effective to obtain viral clearance when combined with IFN and GM-CSF. About 70% to 90% of patients may experience a decrease in total white blood cells, neutrophils, and platelet counts under IFN therapy. Among them, the decrease in neutrophil counts is the most common. The doses of IFN need to be adjusted when the decrease reaches a certain level. GM-CSF can increase the levels of white blood cells and neutrophils to help maintain the effective doses and durations of IFN, thereby improving patients’ compliance, so it is widely used in patients with hepatitis B and C during IFN treatment.

However, the combination antiviral therapy of IFN and GM-CSF is limited to clinical experience and small sample reports. How to standardize the treatment, what indicators should be used to optimize clinical practice, or how to enhance the effect of IFN? There remains a lack of large-sample multi-center standardized clinical data.

[name] from the First Hospital of Peking University designed the Y-type PEGylated recombinant human IFN alpha 2b combined with GM-CSF therapy for HBeAg-positive CHB in a multi-center, randomized, parallel controlled clinical trial in 2014. Using recombinant human Peg-IFN-α-2b (Pegabine®) as the parallel control, they preliminarily explored the treatment efficacy and safety of Peg-IFN combined with GM-CSF in HBeAg-positive CHB patients and compared the medication compliance of Peg-IFN in the two treatment plans as well, to provide a basis for standardizing the combinational therapy. The project has been reviewed by the ethics committee and multi-center clinical study is being carried out nationwide. The main target population is naïve CHB patients with HBeAg positivity, while NA-treated patients are excluded from the project.

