# 4. Study design

## Overview of study design

This study is a multi-center, randomized, prospective, open-label Phase IV clinical trial (Fig 1), CHB patients who had HBV DNA<1000 copies/ml and HBsAg<3000 IU/ml by NAs treatment, were randomized at a ratio of 1:1:1 to one of 3 groups as follows:

Arm A: ETV 0.5mg once daily for 96 weeks

Arm B: Peg-IFN-α-2b 180 ug/week S.C. for 96 weeks plus ETV 0.5mg once daily from day 1 to 48 weeks

Arm C: Peg-IFN-α-2b 180 ug/week S.C. for 96 weeks plus ETV 0.5mg once daily from day 1 to 48 weeks plus GM-CSF from day 1 to 48 weeks

[figure not shown]

Fig 1. Study design

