## Statistical methods

### Primary Variables

The primary efficacy parameter is HBsAg loss at end of treatment and 24 weeks after the end of treatment. Subjects with missing values for this parameter will be considered non-responders.

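### Section 7.8 lets an unblinded investigator take patients out of the study, not only off treatment, without securing HBsAg at calendar Weeks 96 and 120, and a missing value then counts as failure

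*Protocol*

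**What the plan says.** The trial is open-label: "This study is a multi-center, randomized, prospective, open-label Phase IV clinical trial".

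Section 7.8 (Criteria for premature withdrawal) begins with patients who stop study treatment by their own choice. It then turns to leaving the study: "The investigator may withdraw subjects from the study in the event of intercurrent illness, AEs, pregnancy, lack of compliance". It adds two further grounds: that follow-up is impossible, or that "it is in the best interest of the subject to be terminated from the study". The same section cautions: "An excessive rate of withdrawals can render the study non-interpretable; therefore, unnecessary withdrawal of subjects should be avoided".

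Three provisions ask for data from patients who stop early:
- Section 7.4 (Clinical assessments and procedures) asks anyone who discontinues study treatment to return for the Week 96 set of assessments. It does not say when.
- Section 7.8 states the same visit as a preference for patients who refuse further treatment.
- Section 7.8 asks, where possible, for a full final evaluation when a patient leaves the study.

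The synopsis gives the primary endpoint as "HBsAg loss at Week 96". Section 10.2.1 (Primary Variables) states: "The primary efficacy parameter is HBsAg loss at end of treatment and 24 weeks after the end of treatment". It continues: "Subjects with missing values for this parameter will be considered non-responders". Section 10.2.4 (Analysis populations) classes every withdrawn patient in the mITT analysis as a non-responder, whatever the reason, with no exception for a patient whose HBsAg was measured.

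**The concern.** HBsAg is a central-laboratory blood test. An adverse event, a missed injection or a pregnancy does not in itself prevent a sample at Week 96 or Week 120. If the investigator uses one of these grounds to end participation, an obtainable primary outcome may be lost and is then scored as a failure. The decision is taken with the arm known.

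The loss is unlikely to be even. The Background expects falls in blood counts in 70% to 90% of patients on interferon, whereas Group I continues a drug that its patients have already taken for at least a year. Scoring removals as failures pulls down the Peg-IFN rates, while the ETV arm, with 0-3% assumed, has little to lose. The Background also says that GM-CSF can "help maintain the effective doses and durations of IFN" and so improve compliance. Removal could therefore differ between Groups II and III, and a difference in HBsAg loss between them could partly reflect who was kept in the study.

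An analysis plan cannot recover a sample that was not taken, so the rule has to be settled in the protocol.

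**Working it through.** **What happens to a patient removed under section 7.8**

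1. The ground may be one where follow-up is still possible. Section 7.8 lists impossible follow-up as only one alternative among several.
2. The section 7.4 visit is triggered by stopping treatment. Nothing states that it applies after removal from the study, or that it takes place at calendar Week 96.
3. The section 7.8 final evaluation takes place at removal, which may be long before Week 96. Follow-up after removal for an adverse event runs, where possible, until the event resolves. Neither secures HBsAg at Week 96 or 120.
4. Under the synopsis definition an early value is not a Week 96 value. Under the section 10.2.1 definition it might pass as the patient's own end of treatment, but a second value 24 weeks later would still be needed. Whatever is missing becomes a non-response.
5. In the mITT analysis, section 10.2.4 makes the patient a non-responder even if a value was obtained.

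**Inputs for the size**

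- Arm size: 257 / 3 = 85.7, taken as 86.
- ETV rate: 0-3% (Numbers of Patients; Sample Size).
- Peg-IFN rate: 13%, which is 3% plus the 10-point gain expected in the Background. It lies within the 10-20% of Numbers of Patients but above the 3-10% of Sample Size.
- Assumed: removal of 10% or 20% of a Peg-IFN arm and none of the ETV arm, no usable HBsAg after removal, two-sided 5%, uncorrected chi-square, exact binomial power.

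The protocol derives its 80-100 per group from no stated power or dropout, so there is no figure of its own to reproduce.

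**Peg-IFN v ETV**

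If removed patients have the same true rate, observed rate = true rate × (1 − share removed): 13% × 0.9 = 11.7%; 13% × 0.8 = 10.4%.

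| ETV rate | None removed (13%) | 10% removed (11.7%) | 20% removed (10.4%) |
|---|---|---|---|
| 3% | 70.4% | 60.3% | 48.9% |
| 1% | 92.6% | 88.0% | 81.3% |
| 0% | 99.7% | 99.3% | 98.3% |

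If removed patients have half the true rate, the observed rates are 13% × 0.95 = 12.35% and 13% × 0.90 = 11.7%. At ETV 3% power is then 65.5% and 60.3%.

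A separate normal-approximation check used ETV 3%, with 20% of Peg-IFN and 2% of ETV patients removed. Power falls from 46.1% to 30.7% at a true 10%, from 79.0% to 62.0% at 15%, and from 94.4% to 83.9% at 20%.

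**Group III v Group II**

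Assume an equal true rate of 15%, with 15% removed in Group II and 5% in Group III. The observed rates are 15% × 0.85 = 12.75% and 15% × 0.95 = 14.25%, a difference of 1.5 points. The test rejects in 5.8% of trials, against 4.8% when both rates are 15%. With 20% v 5% removed and true rates of 10% to 20%, the difference is the true rate × 0.15, that is 1.5 to 3.0 points.

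**The case against.** A reader might infer that HBsAg is never drawn after removal. The documents do not support that: section 7.4 asks for the Week 96 assessments after treatment stops, the schedule places HBsAg in that visit, and section 7.8 asks for a final evaluation. What stands is that the draw may be early and is not guaranteed.

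A reader might also infer that the rule creates every missing value. It does not. Where follow-up is impossible, or a patient fails to attend visits, the value would probably be missing anyway.

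Other sections point towards stopping treatment rather than leaving. After four missed doses the stated consequence concerns further study drug. A pregnant patient leaves the treatment period and is still monitored. The concomitant-medication section foresees follow-up after permanent discontinuation. Section 7.8 is permissive, requires reasons to be documented and discourages unnecessary withdrawal. This makes wide use of the clause less likely, but it leaves the clause open.

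The arm imbalance is an inference from the Background, since no arm-level withdrawal rate is given. The power loss depends heavily on the ETV rate and nearly vanishes at 0%. The table also treats every removal as recoverable, so it shows the most the fix could regain at those shares.

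Better compliance is part of how GM-CSF is meant to work, so counting withdrawal as failure could be a deliberate composite endpoint. That is a fair position, but the protocol defines the primary endpoint as HBsAg loss and states no such composite.

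The point also overlaps with the timing of the section 7.4 visit and the scoring rule in section 10.2.4. Clarifying those alone would not be enough, because a patient taken out of the study is no longer covered by a visit rule for those who stop treatment.

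**Conclusion.** The concern holds in a limited form. As written, the protocol permits an arm-aware removal from the study while the primary outcome is still obtainable, does not secure HBsAg at Weeks 96 and 120 afterwards, and scores the gap as failure.

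Against ETV this is conservative, so it does not support an inference that benefit of Peg-IFN would be falsely claimed. The cost is power: about 10 to 21 points at ETV 3% with 10% to 20% removed (70.4 − 60.3 = 10.1; 70.4 − 48.9 = 21.5), about 5 to 11 points at ETV 1% (92.6 − 88.0 = 4.6; 92.6 − 81.3 = 11.3), and at most 1.4 points at ETV 0%. Between Groups II and III the distortion is small, about 1.5 points in the assumed scenario. It does fall on the comparison with least prior data.

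All removal shares and their split between arms are assumptions. The change is worth making because it is cheap and the lost data cannot be recovered later.

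**What to change.** 1. In section 7.8, keep the listed grounds but separate the two consequences. By default, a decision based on adverse events, illness, pregnancy, non-compliance or best interest ends study treatment only. Study exit is reserved for withdrawn consent, death, loss to follow-up, or a documented judgement that further follow-up is impossible or against the patient's interest. The best-interest protection therefore stays.
2. In sections 7.4 and 7.8, state that patients off treatment still have HBsAg drawn at calendar Weeks 96 and 120.
3. Align sections 10.2.1 and 10.2.4: a measured value is analysed as measured, in ITT and mITT alike, and non-responder imputation applies only to values not obtained.
4. Record who initiated each study exit and why, by arm.

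No clinical stopping rule changes. The cost is a short amendment, two draws that are already scheduled, and modest site effort to recall patients who are off treatment.

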# Schedule of investigation medical product

## Stopping rules

Individual subject will be stopped in the event of any of the following:

- Severe hypersensitivity reactions (e.g., anaphylaxis, angioedema, bronchoconstriction) • Evidence of hepatic decompensation, e.g., significant deterioration in hepatic function including those requiring alternative therapies
- Severe depression
- Convulsions
- Thyroid abnormalities that cannot be adequately treated
- Hypoglycemia, hyperglycemia, or diabetes mellitus that cannot be effectively controlled by medication
- New or worsening visual disorders such as field deficits, decreased or loss of vision
- Persistent or unexplained pulmonary infiltrates or pulmonary function impairment
- Worsening of psoriatic lesion
- Development of autoimmunity, including autoimmune hepatitis
- Renal failure, including creatinine >100 μmol/L
- Severe symptoms e.g., rigors
- Absolute neutrophil count < 0.25 × 10 ^9^cells/L or febrile neutropenia
- Platelets < 25 × 10 ^9^ cells/L
- Pregnancy

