## Dosing Regimen

The dose of Peg-IFN-α-2b will be 180ug, administered S.C. once per week, for 96 weeks in group II and group III. The dose of ETV will be 0.5mg P.O. once per day, for 96 weeks in group I, for 48 weeks in group II and group III. GM-CSF will be administered S.C. a 5-day treatment of GM-CSF every 4 weeks, starting from the 1st day of the 1st week, 75ug once per day, periodically until 48 weeks in group III.

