## Concomitant medication and treatment

Use of any investigational drugs as a result of participation in another clinical study is prohibited during the study including the extended long-term follow-up period.

Concomitant use of any other investigational drugs (e.g., compassionate use), immunomodulatory treatments (e.g., systemic corticosteroids), growth factors (e.g., erythropoietin) or antiviral treatments with anti-HBV activity (e.g., lamivudine, tenofovir, emtricitabine, adefovir, telbivudine, systemic acyclovir, systemic famciclovir) other than those specifically allowed by this protocol are prohibited during either the treatment period or follow-up, in order to minimize the confounding effects of such treatments in determining treatment responses.

Exceptions to this are as follows:

Subjects with significant deterioration in hepatic function who permanently discontinue study drug and need to consider NA therapies in group II and group III, treatments with anti-HBV activity will not be prohibited during follow-up period.

Herbal, botanical, and other agents that are traditionally used for chronic HBV disease are discouraged.

All concomitant medications should be reported to the investigator and recorded on the appropriate electronic Case Report Form (CRF), including details of any previous anti-HBV treatment, as well as any other previous concomitant medications taken within 6 months

prior to baseline.

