### Warnings and precautions

IFN may cause or aggravate fatal or life-threatening neuropsychiatric, autoimmune, ischemic, and infectious disorders. Subjects should be monitored closely with periodic clinical and laboratory evaluations. Therapy should be withdrawn from subjects with persistently severe or worsening signs or symptoms of these conditions. In many, but not all cases, these disorders resolve after stopping IFN therapy.

There are no adequate, controlled studies of any IFN in pregnant females. Therefore, extreme care must be taken to avoid pregnancy during the study in female subjects, and female partners of male subjects taking IFN. Females who are pregnant or breast-feeding will be excluded. A pregnancy test will be performed for each female of childbearing potential prior to baseline and be performed according to the schedules in Table 1.

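### The only exception to the ban on other anti-HBV drugs (section 7.7) leaves out Group I and, on one reading of section 8.1, Group II/III patients whose entecavir is stopped early

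*Protocol*

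**What the plan says.** Section 8.1 (Stopping rules) begins "Individual subject will be stopped in the event of any of the following" and applies to all three groups. One listed event is "Evidence of hepatic decompensation, e.g., significant deterioration in hepatic function including those requiring alternative therapies". No item says which study drug stops, or whether the patient leaves treatment or leaves the study.

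Section 4.4 (Dosing Regimen) gives ETV "for 96 weeks in group I, for 48 weeks in group II and group III". ETV is therefore the only study drug in Group I, and one of two or three study drugs in Groups II and III until Week 48.

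Section 7.7 (Concomitant medication and treatment) says that anti-HBV treatments "other than those specifically allowed by this protocol are prohibited during either the treatment period or follow-up". One exception bears on anti-HBV drugs. It concerns "Subjects with significant deterioration in hepatic function who permanently discontinue study drug and need to consider NA therapies in group II and group III", for whom "treatments with anti-HBV activity will not be prohibited during follow-up period".

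**The concern.** Sections 7.7 and 8.1 do not fit together. Section 8.1 expects that some patients in any group will be stopped for failing liver function and will need another therapy. Section 7.7 permits that therapy only in Groups II and III.

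Section 7.7 also makes no provision for a Group II/III patient who loses ETV before Week 48 because of another drug's toxicity and whose liver function is intact. All entrants are suppressed after at least one year of ETV (section 6.3), and the Background refers to relapse when therapy is stopped.

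What is at stake is patient safety and consistent conduct across six centers.

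**Working it through.** No power, alpha or rate enters this point. The check sets the stopping rule against the concomitant-drug rule, case by case.

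**Inputs**
- Stop events in section 8.1: 15, of which 0 name a drug.
- Events that the protocol itself ties to interferon: 4. Severe depression and autoimmunity come under the warning in section 9.3.4 that "IFN may cause or aggravate fatal or life-threatening neuropsychiatric, autoimmune, ischemic, and infectious disorders". Low neutrophils and low platelets are linked to interferon in the Background. Visual disorders are a possible fifth, by inference from the eye examinations required for interferon-treated patients in section 7.4.2.
- Planned ETV: 96 weeks in Group I and 48 weeks in Groups II/III (section 4.4).
- Conditions of the section 7.7 exception, all required: Group II or III; significant hepatic deterioration; permanent discontinuation; during follow-up.

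**Cases**

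| Case | Meets the section 7.7 exception? | NA permitted while on study? |
| --- | --- | --- |
| Group I, stopped for hepatic decompensation, kept on study | No, group not named | None; the stopped drug is its ETV |
| Group II/III, stopped for hepatic deterioration | Yes, in follow-up | Yes |
| Group II/III, stopped for a non-hepatic event, liver deteriorates later | Yes, in follow-up; the exception turns on the patient's condition, not on the reason for the stop | Yes |
| Group II/III, non-hepatic stop before Week 48, only Peg-IFN or GM-CSF stopped | Not needed | Yes, scheduled ETV to Week 48 |
| Group II/III, non-hepatic stop before Week 48, all drugs stopped, kept on study, no hepatic deterioration | No | None |
| Any group, withdrawn from the study | Not needed | The ban no longer binds |

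Two rows end with no permitted NA: the Group I row, and the Group II/III row in which every drug stops and the patient stays on study.

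**Size of the second gap, on that reading only**

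Scheduled ETV lost in Groups II/III = 48 − stop week. For an illustrative stop at Week 4, 48 − 4 = 44 weeks. From Week 48 onward it is 0, because ETV has ended by design.

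**Start of follow-up**

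Sections 5.1.1 and 7.4 count follow-up from the end of treatment. The natural reading is that it begins when the patient's treatment ends, so the exception does not delay rescue for Group II/III hepatic cases.

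**The case against.** A reader might infer that the protocol orders ETV to be stopped whenever Peg-IFN causes harm, leaving the patient uncovered. The documents do not support that.
- Section 8.1 names no drug, so it does not order ETV to stop.
- ETV is not among the drugs that section 7.7 gives as examples of the ban. Up to Week 48 it can be read as a treatment the protocol allows.
- Section 9.3.4 speaks of stopping interferon, and the Background speaks of adjusting the interferon dose when counts fall. Both point to acting on Peg-IFN.
- Sections 7.8 and 9.2.5 offer exits, through withdrawal or through leaving the test regimen when an excluded drug is needed. Section 7.8 adds that "An excessive rate of withdrawals can render the study non-interpretable; therefore, unnecessary withdrawal of subjects should be avoided", but withdrawing a patient who needs an NA is not unnecessary.
- Every Group II/III patient stops ETV at Week 48 anyway, so an early stop brings a planned state forward. The 12-week interval between scheduled HBV DNA tests applies to everyone and is not caused by the stopping rule.

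All of this stands, and it confines the Group II/III gap to one reading out of three. It does not remove the Group I gap. There ETV is the only study drug, so no other drug can be stopped in its place, and the exception as written excludes the group. The exits in sections 7.8 and 9.2.5 do help a Group I patient, but only by leaving the study or the test regimen. Neither lifts the section 7.7 ban for a patient who stays on study.

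**Conclusion.** The point holds as a minor safety and conduct issue. The section 7.7 exception is a stated rule that is too narrow when followed as written.

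The Group I omission follows directly from the text, for a patient who stays on study after the stop. The Group II/III omission is conditional: it needs a stop before Week 48, all study drugs stopped, the patient kept on study, and no hepatic deterioration. A Group II/III patient stopped for another reason whose liver later deteriorates is already covered in follow-up.

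The protocol gives no stopping rates, so the number of patients affected cannot be estimated. A reader might also infer bias in the HBsAg comparison. Nothing in the document shows it, and none is claimed.

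**What to change.** In section 7.7, allow NA therapy in any group from the date of permanent discontinuation, in the treatment period or in follow-up, for hepatic deterioration or when ETV was stopped early. Record its start date.

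In section 8.1, state that when the investigator judges an event due to Peg-IFN or GM-CSF, that drug stops and ETV continues as scheduled (to Week 48 in Groups II/III). All study drugs stop for pregnancy, in line with section 9.3.3, or where ETV is suspected. Section 8.2 needs no change.

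The cost is a few sentences. Concomitant drugs and treatment stops are already recorded (sections 7.7 and 7.6), and no visits, tests or patients are added. Section 9.2.3 records a single yes or no on relatedness to study drug. The fix can rest on clinical judgement, but documenting attribution drug by drug would be new data capture.

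The downside is some NA use among early stoppers, which should be reported alongside HBV DNA and ALT.
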